# Modifying exercise and physical therapy in medical rehabilitation to promote a physically active lifestyle: Protocol for a multicenter controlled hybrid type 2 effectiveness-implementation study in three German rehabilitation centers

**DOI:** 10.1186/s13102-025-01179-2

**Published:** 2025-05-28

**Keywords:** Co-creation, Health promotion, Physical activity, Physical activity-related health competence, Physical literacy, Health literacy

## Abstract

**Introduction:**

Since rehabilitation programs often do not enhance long-term physical activity in persons with a health condition, there is a great need to arrange rehabilitation concepts towards a stronger emphasis on sustainable physical activity promotion. In this regard, the model of physical activity-related health competence (PAHCO) offers the potential for optimizing physical activity promotion. In the context of medical rehabilitation, the STABEKO study uses a co-creation approach to modify existing exercise and physical therapy according to PAHCO and long-term physical activity promotion in three rehabilitation centers in Bavaria, Germany. The objectives of the STABEKO study are A) to evaluate the implementation of modified exercise and physical therapy and to identify influencing factors for development and implementation, and B) to determine the short- and long-term effectiveness of the modified therapy on PAHCO and physical activity of the persons undergoing rehabilitation.

**Methods:**

As part of the STABEKO study, we will use cooperative planning as a co-creation approach for planning, developing, and implementing actions to modify exercise and physical therapy by engaging relevant actors from practice, policy, and research in an equal decision-making process. Within a multicenter controlled hybrid type 2 effectiveness-implementation study, we will simultaneously evaluate the effectiveness and implementation of modified exercise and physical therapy by collecting, analyzing, and triangulating qualitative and quantitative data at several measurement time points.

**Discussion:**

The STABEKO study will provide comprehensive insights into the implementation and effectiveness of exercise and physical therapy in medical rehabilitation, modified using a co-creation approach to promote long-term physical activity of persons undergoing rehabilitation. While the implementation study will indicate which modifications could be achieved and which factors have influenced their development and implementation, the effectiveness study will investigate whether modified exercise and physical therapy lead to changes in PAHCO and physical activity in persons undergoing rehabilitation. The results of this study will determine the dissemination of long-term physical activity promotion in the German rehabilitation sector and will provide important information for modifying existing therapeutic concepts to improve their effectiveness and implementation at an international level.

**Trial registration:**

The study was registered on the Open Science Framework on July 8 2024: 10.17605/OSF.IO/2N8UM and 10.17605/OSF.IO/J3KR2.

**Supplementary Information:**

The online version contains supplementary material available at 10.1186/s13102-025-01179-2.

## Introduction

Rehabilitation as a health strategy aims to optimize the functioning of people living with a health condition [1, 2]. This includes reducing the impact of health conditions on the daily lives of people affected and supporting them in remaining as independent as possible and participating in education, work, and meaningful life [3]. Behavioral change in physical activity (PA) is key to achieving these rehabilitation aims, as regular PA positively influences individuals’ exercise capacity and health-related quality of life for more than 25 health conditions [4]. Despite these benefits, individuals with a health condition show considerably lower PA levels compared to healthy adults [5, 6]. This makes exercise and physical therapy a central component of a rehabilitation program, especially as modern rehabilitation guidelines highlight the importance of physical activity promotion (PAP) [7–9]. However, increasing PA levels in people with health conditions is a major challenge, and sustainable changes toward a physically active lifestyle after rehabilitation are often rather limited [10].

The model of physical activity-related health competence (PAHCO) [11, 12] offers the potential for optimizing PAP in medical rehabilitation. The PAHCO model explicitly addresses “competencies” for physically active lifestyles, also in the (health) educational sense [13]. As such, the PAHCO model incorporates three major components, which are formed by the interplay of basic elements (Fig. 1). The framework posits that individuals require (i) movement competence, (ii) self-regulation competence, and (iii) control competence to execute PA in a health-oriented way. First, *movement competence* bundles the motor-related requirements to partake in planned, structured exercise (e.g., individual workout, leisure-time team sport) and to accomplish activities of daily living (e.g., cycling to work, gardening, household). Second, *self-regulation competence* ensures the regularity of PA (e.g., its frequent initiation and the duration that has to be maintained) by providing the necessary motivational and volitional resources (e.g., self-efficacy, PA-specific self-control). Third, *control competence* detaches from a mere orientation on quantity and guarantees that PA meet quality aspects by aligning with individual’s biopsychosocial health. This model component is based on aspects of knowledge, self-reflection, and understanding, which together ensure, for example, that physical stresses do not fall below or exceed thresholds of biopositive adaptation (i.e., physical health) and that activity modalities are selected that allow positive affective responses to PA (i.e., psychosocial health).

**Fig. 1 Fig1:**
[figure not shown]
The physical activity-related health competence (PAHCO) model [11, 12]

In summary, PAHCO overcomes the isolated functional orientation of PA by connecting “training and exercising” with “holistic individual learning” as well as “authentic experiencing” in contexts relevant for PA [11, 14]. Due to its long-term horizon, such a concept can make a pivotal contribution to sustainable rehabilitation success. In particular, the model can serve as a guide for exercise and physical therapy approaches with a focus on PAP. The model has found its way into the framework concepts of German rehabilitation standards [15]. However, recent analyses of the national rehabilitation landscape have illustrated that a minority of current exercise-related concepts and therapeutic practices within rehabilitation centers comply with the sustainable, empowering idea of PAHCO [16, 17]. The causes for this finding are manifold and mainly relate to the organizational-structural level (e.g., limited freedom for PA-promoting therapy due to rigid standard prescriptions, insufficient structures and processes for interprofessional collaboration) and the personal level (e.g., partly limited knowledge, skills, and abilities of therapists regarding PA-promoting therapy, low acceptance of PA-promoting therapy among persons undergoing rehabilitation) [18].

Accordingly, there is a great need to arrange rehabilitation concepts with a stronger emphasis on PAP. In this regard, the use of a co-creation approach appears promising, as the collaboration of researchers and non-academic actors facilitates the development and implementation of new actions that fit the setting and its individuals by taking into account the existing constraints and needs in such a way that these can be accepted and sustainably anchored within the system [19–21]. Several studies have demonstrated the successful application of co-creation approaches to improve health services and PAP in different settings [22–25], and the potential has also been addressed in the context of the rehabilitation system [26, 27]. Cooperative planning (CP) corresponds to such a co-creation approach and engages relevant actors from practice, policy, and research in an equal decision-making process to plan, develop, and implement actions to PAP [24, 28–31]. As a previous study from vocational education and training has shown that PAHCO, as a complex concept for PAP, was successfully adopted via CP [32], it appears worthwhile to use this approach to optimize PAP in medical rehabilitation. Therefore, the STABEKO study uses CP to modify exercise and physical therapy according to PAHCO and long-term PAP in three rehabilitation centers in Bavaria, Germany, to promote long-term PA in persons undergoing rehabilitation.

Following the structure of a type 2 hybrid effectiveness-implementation study [33, 34], the study “Partizipative Weiterentwicklung und Implementierung einer kompetenzorientierten Bewegungstherapie in der medizinischen Rehabilitation zur **Stä**rkung der **be**wegungsbezogenen Gesundheits**ko**mpetenz von Rehabilitand*innen” (STABEKO; Eng.: Participatory development and implementation of competence-oriented exercise and physical therapy in medical rehabilitation to strengthen PAHCO of persons undergoing rehabilitation) aims to simultaneously and equally evaluate the effectiveness and implementation of exercise and physical therapy in medical rehabilitation, modified by using CP. Specifically, the research objectives are as follows:

A) To evaluate the implementation of modified exercise and physical therapy achieved via CP and to identify influencing factors for development and implementation;

B) To determine the short- and long-term effectiveness of modified exercise and physical therapy achieved via CP on PAHCO and PA of persons undergoing rehabilitation.

## Methods

The present study protocol follows the Standard Protocol Items: Recommendations for Interventional Trials (SPIRIT) guidelines [35]. The SPIRIT checklist is provided in the supplementary material (see Supplementary Material 1). In combination with the present study protocol, the final reports will follow the Standards for Reporting Qualitative Research [36] for the implementation study, the 2010 Consort Statement [37] for the effectiveness study, and the Standards for Reporting Implementation Studies (StaRI) Statement [38] for the entire hybrid effectiveness-implementation study.

### Study design and setting

We will simultaneously evaluate the effectiveness and implementation of modified exercise and physical therapy within a multicenter non-randomized controlled trial. The study will take place in three inpatient rehabilitation centers in Bavaria, Germany, between September 2023 and May 2027. These rehabilitation centers are part of the clinic association of the German Pension Insurance (Ger.: Deutsche Rentenversicherung) in Bavaria, Germany, with a specialization in indications in the fields of orthopedics, rheumatology and/or internal medicine. According to the tenth revision of the International Statistical Classification of Diseases and Related Health Problems (ICD-10) [39], examples of health conditions treated in these clinics include type 2 diabetes mellitus (E11), obesity (E66), coxarthrosis (M16), gonarthrosis (M17), cervical disc disorders (M50) other intervertebral disc disorders (M51), other dorsopathies (M53), dorsalgia (M54), and shoulder lesions (M75). The rehabilitation centers confirmed their willingness to participate in this study in a letter of intent. The corresponding costs for the personnel resources required to complete the study are included in the funding requested and are provided to the rehabilitation centers.

### Study procedure

Within the STABEKO study, we will use CP as a co-creation approach to modify exercise and physical therapy in medical rehabilitation. More specifically, CP engages relevant actors from practice, policy, and research in an equal decision-making process to plan, develop, and implement actions to modify exercise and physical therapy [24, 28, 29, 31]. The study procedure will consist of the following four phases for each rehabilitation center: preparation phase, development phase, implementation phase, and maintenance phase (see Fig. 2).

**Fig. 2 Fig2:**
[figure not shown]
Overview of the study design

The study procedure will start with a four-month *preparation phase*, in which the researchers familiarize themselves with the rehabilitation center, its organizational structures and processes, the persons undergoing rehabilitation, and identify relevant actors for joining a CP group. Therefore, initial meetings between actors from research, practice, and policy will take place, serving the presentation of the study procedure. In addition, a detailed explorative situation analysis will be carried out using mixed methods to obtain relevant information about the respective rehabilitation center (e.g., therapeutic concept, staff, organizational structures and processes) and its persons undergoing rehabilitation, which will be incorporated into the subsequent development phase.

The eight-month *development phase* is the centerpiece of CP. In this phase, four to six CP meetings will take place to jointly develop actions for modifying the existing exercise and physical therapy according to PAHCO and long-term PAP within the scope of a CP group. The CP group will consist of various actors from research (i.e., researchers), practice (e.g., exercise therapists, physical therapists, physicians, psychologists, social workers, administrative staff), and policy (e.g., clinic directors). While the researchers will provide the current scientific findings, moderate, and supervise the CP meetings, the actors from practice and policy will contribute their views and suggestions for modifying exercise and physical therapy and share their opinions on the opportunities for implementation. This phase will encompass the following steps in accordance with current recommendations for CP [28, 40]: (1) brainstorming of ideas and suggestions, (2) categorization of ideas and suggestions, (3) prioritization of suggestions, (4) definition of actions, (5) specification and finalization of actions, and (6) initiation. First, initial ideas for possible actions to modify exercise and physical therapy according to PAHCO and long-term PAP will be gathered based on the available scientific evidence and the results of the detailed explorative situation analysis. Potential starting points will be the therapy concept, human resource development, and organizational development. These ideas will subsequently be categorized and prioritized, taking into account their perceived attractiveness, relevance, and feasibility. In the following, concrete actions to modify exercise and physical therapy will be developed based on the prioritized ideas. These actions will be documented in an action plan that contains a detailed description of the content to be implemented along with the intended implementation, including the associated realization steps (e.g., the requirements to be fulfilled, the defined time frame and responsibilities). Finally, this action plan will be discussed, reflected, and finalized through repeated adjustments.

In the *implementation phase*, which lasts four months, the modified exercise and physical therapy will be implemented in accordance with the action plan under the responsibility of practitioners, with researchers providing advice and support. This will be followed by the *maintenance phase*, in which the modified exercise and physical therapy should be continued regularly and permanently.

Parallel to the abovementioned phases, we will evaluate implementation and effectiveness by collecting and analyzing qualitative and quantitative data at several measurement time points (for more details, see Implementation study or Effectiveness study). The study procedure will not be simultaneously launched in the participating rehabilitation centers; rather, the centers will be successively integrated with a 5-month delay to benefit from the experience previously gained. The STABEKO study will be monitored and supervised by an expert panel comprising various external actors (e.g., representatives of the German Pension Insurance [Ger.: Deutsche Rentenversicherung] in Bavaria, members of the exercise and physical therapy working group of the German Society for Rehabilitation Sciences [Ger.: Deutsche Gesellschaft für Rehabilitationswissenschaften e.V.], and representatives of the German Association for Health Sport and Sport Therapy [Ger.: Deutscher Verband für Gesundheitssport & Sporttherapie e.V.]).

### Implementation study

The implementation study aims to evaluate the implementation of modified exercise and physical therapy achieved via CP and to identify influencing factors for development and implementation by collecting, analyzing, and triangulating data following a mixed methods approach.

#### Outcomes

To evaluate the implementation of modified exercise and physical therapy, the modifications that were developed within the development phase and defined in the action plan (see Study procedure) will be examined. For this purpose, we will investigate the concept of modified exercise and physical therapy, the implementation status of the modifications, and patient-reported experience measures (PREMs). To evaluate the factors influencing the development and implementation of modified exercise and physical therapy, we will assess the CP meetings as well as the facilitators and barriers to development and implementation. Table 1 provides an overview of the evaluation outcomes, data sources, and measurement time points of the implementation study.

**Table 1 Tab1:** Overview of data to be collected in the implementation study

Evaluation outcome		Data source		Measurement time points		
			Preparation phase	Development phase	Implementation phase	Maintenance phase
Implementation of modified exercise and physical therapy	Concept of modified exercise and physical therapy	Action plans			X	
	Implementation status of modifications	Self-developed questionnaire			X	X
	Patient-reported experience measures	Self-developed questionnaire	X			X
	Additional information on modified exercise and physical therapy	Semi-structured interviews			(X)	(X)
Influencing factors for development and implementation of modified exercise and physical therapy	Cooperative planning meetings	Structured minutes		X		
	Facilitators and barriers	Semi-structured interviews			X	X

#### Data collection

To evaluate the implementation of modified exercise and physical therapy, an initial document analysis of the action plan will be conducted in the implementation phase to gain an understanding of the concept of modified exercise and physical therapy (e.g., number and content of developed actions for modifications). Next, the implementation status of the modifications will be assessed in both the implementation and maintenance phases via a self-developed questionnaire. An exemplary question on the implementation status is: “To what extent has the modification been implemented as defined in the action plan?” Data will be collected analogously via a paper-pencil questionnaire. Following a purposeful sampling of information-rich cases [41], we will invite the main actors of each rehabilitation center to participate in this questionnaire survey in the respective implementation and maintenance phases. In addition, the PREMs will be conducted in the development phase and maintenance phase via a self-developed questionnaire to assess the experiences of the persons undergoing rehabilitation with exercise and physical therapy before and after the modification. An exemplary item of the PREMs, answered on a five-point Likert scale, is “During exercise and physical therapy, I received helpful information on how and where I can remain physically active independently after rehabilitation.” This questionnaire will be part of the effectiveness study’s data collection at the end of medical rehabilitation (T1) (see Effectiveness study).

To identify the factors influencing the development and implementation of modified exercise and physical therapy, structured minutes of all CP meetings will be taken during the development phase. These will contain information about the date and duration of the CP meetings, the participants, and the most important topics discussed. In addition, the facilitators and barriers for development and (long-term) implementation will be determined through semi-structured interviews. We will develop an interview guide based on the domains of the Consolidated Framework for Implementation Research (CFIR) [42, 43] and inspired by the explorative situation analysis conducted in the preparation phase. An exemplary question for identifying the influencing factors is “What contributed to the modification(s) being implemented / not being implemented?” In addition, the interviews will allow us to obtain additional information about the developed modifications, if required. In accordance with purposeful sampling of information-rich cases [41], we will again invite the main actors of each rehabilitation center (as described above for the questionnaire survey) to participate in an interview in the respective implementation and maintenance phases. One interview per participant will be conducted and audio-recorded either face-to-face, by telephone or video call.

#### Data management

The analog questionnaire data will be digitalized and then stored and processed in SPSS (IBM, Armonk, USA). The structured minutes will be saved on local drives. The audio-recorded interviews will be transcribed verbatim. For reasons of anonymity, we will replace personal names with professional titles as well as names of rehabilitation centers and cities with pseudonyms. The interview data will be stored and analyzed using MAXQDA (VERBI Software, Berlin).

#### Data analysis

The data collected in the course of the implementation study will be analyzed depending on the type of data source used. The document analyses of action plans and structured minutes will draw on a qualitative content analysis [44] and will be performed using MAXQDA (VERBI Software, Berlin). Data from the questionnaire survey on the implementation status and PREMs will be analyzed descriptively by using SPSS (IBM, Armonk, USA). The interview transcripts will be analyzed via qualitative content analysis [44], which includes a deductive and inductive definition of categories. This data analysis encompasses the following steps: (1) initial text work, (2) deductive development of the main categories based on the interview guide, (3) coding of the entire material according to the main categories, (4) compilation of all coded text passages of the same main category, (5) inductive definition of subcategories based on the transcribed material, (6) coding of the entire material according to the refined categories, and (7) evaluation and interpretation [44]. Two researchers will develop and double-check the main categories and subcategories and apply them to the interview transcripts. Inconsistencies will be discussed and resolved within the research team. MAXQDA (VERBI Software, Berlin) will be used for coding and analyzing the interview data.

Upon completion of the separate analyses, the data from the implementation study will be triangulated in the interpretation phase to provide a comprehensive description of the modifications developed and implemented and the factors influencing development and implementation [45]. In addition, the findings of the explorative situation analysis conducted in the preparation phase may be used to explore the modifications and influencing factors in more detail. Additionally, the results of the implementation study could be used to interpret the results of the effectiveness study.

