#### Sample size

With the three PAHCO dimensions (i.e., movement competence, control competence, and self-regulation competence), the present study lists three main outcomes. We set *p* ≤.05 for the repeated multivariate analyses of covariance (MANCOVA) and assume a pre-post correlation (within-subjects factor) of *r* = .40, as a previous study revealed an autoregressive *r* = .418 [52]. To detect a significant intervention effect of medium magnitude (*η*^2^ = 0.04; *f* = 0.20) paired with a statistical power ≥ 80%, we must recruit a total of 244 persons undergoing rehabilitation. Given the number of rehabilitation centers (*n* = 3), we are advised to aim for 82 participants per center. Since each rehabilitation center includes persons undergoing rehabilitation at two time periods, that is, before modification (i.e., CG) and after modification (i.e., IG), we must recruit a number of *n* = 41 participants per time period in the respective rehabilitation center. Considering a longitudinal dropout rate of 15%, we aim to recruit *n* = 48 participants per time period in each rehabilitation center.

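### The PREMs serve a before/after comparison of two patient cohorts, but the plan commits only to description and names no measure of sampling error for the difference

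*Protocol article*

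**What the plan says.** In the Implementation study, Data collection, the PREMs are a self-developed patient questionnaire used "to assess the experiences of the persons undergoing rehabilitation with exercise and physical therapy before and after the modification". The example item is "answered on a five-point Likert scale". The questionnaire is completed within the effectiveness study's T1 survey at the end of rehabilitation. The respondents are therefore that study's control cohort (usual therapy) and intervention cohort (modified therapy), which are different people recruited in different periods.

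The Implementation study, Data analysis, then gives one method for two instruments: "Data from the questionnaire survey on the implementation status and PREMs will be analyzed descriptively by using SPSS". The other instrument is the implementation-status questionnaire, completed by a purposefully chosen set of main actors at each centre. The same section says that findings from the implementation study may be drawn on when the effectiveness results are interpreted.

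The Sample size section plans for "41 participants per time period in the respective rehabilitation center", raised for dropout to "48 participants per time period in each rehabilitation center".

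**The concern.** Description suits a small, purposefully chosen group of staff. It suits the PREMs less well, because their stated use is a contrast between two independent patient samples, and any such contrast carries sampling error. The article names a method here rather than staying silent, and that method has no component that conveys this error.

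The stake is interpretive. If PAHCO shows no effect, the first question is whether patients noticed a different therapy. If PAHCO improves, a PREM shift will be cited as support. In either case a difference without an interval invites more weight than the data may bear. Implementation is also not a side issue: the Introduction gives it equal standing with effectiveness.

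**Working it through.** **Inputs from the documents**
- Total required: "we must recruit a total of 244 persons undergoing rehabilitation".
- Three centres, two periods per centre, 15% dropout (Sample size).
- Five-point response format (Implementation study, Data collection).

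**Inputs assumed**
- The SD of a PREM item is not given. I take 1.0, with a range of 0.7 to 1.2.
- PREM respondents at T1 number between the evaluable and the recruited targets.
- Patients are independent within centre and period, and the SD is the within-centre SD.

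**Cell sizes, reproducing the plan**
- 244 / 3 = 81.3, taken as 82 per centre; 82 / 2 = 41 per centre and period.
- 244 / 0.85 = 287.1, and 6 × 48 = 288, which agrees with 48 recruited per centre and period.
- Per period over three centres: 3 × 41 = 123 and 3 × 48 = 144.

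The plan gives no precision, hypothesis or power for the PREMs, so there is no PREM figure to reproduce.

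**Half-width of the 95% interval for a difference of two independent means**

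Half-width = 1.96 × SD × √(2/n), with n per group.

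| Reading | n per group | SD 0.7 | SD 1.0 | SD 1.2 |
|---|---|---|---|---|
| One centre | 41 | 0.30 | 0.43 | 0.52 |
| One centre | 48 | 0.28 | 0.40 | 0.48 |
| Pooled | 123 | 0.17 | 0.25 | 0.30 |
| Pooled | 144 | 0.16 | 0.23 | 0.28 |

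Example: 1.96 × 1.0 × √(2/41) = 1.96 × 0.221 = 0.43.

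**What a per-centre decision rule would do**

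Take a true difference of 0.4 points and SD 1.0.
- One centre, n = 41: SE = 0.221 and 0.4 / 0.221 = 1.81. Power is about Φ(1.81 − 1.96) = 44%.
- Pooled, n = 123: SE = √(2/123) = 0.128 and 0.4 / 0.128 is about 3.14. Power is about Φ(3.14 − 1.96) = 88%.

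The pooled estimate is therefore reasonably informative. A verdict centre by centre would miss a real change of this size more often than not.

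**A related point to reconcile**

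Table 1 places the first PREM measurement in the preparation phase, while the Data collection text places it in the development phase. The link to the T1 survey identifies the respondents as the control cohort, but the two places should agree.

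**The case against.** The strongest reply is that nothing here is wrong or contradictory. The only stated hypothesis concerns PAHCO and physical activity. The PREMs are unpowered and self-developed, and they belong to a triangulation meant to describe the modifications. Even the secondary effectiveness outcomes are exploratory. In a condensed article, table layout can be left to the full plan.

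Much of this stands. No significance test is owed, and three stronger readings should be resisted.
- A reader might infer that the PREMs are the only patient-level evidence on whether therapy changed. They are not. Table 2 and the Effectiveness study, Data collection, also provide for a form recording each participant's therapy duration and content at T1. A note to Table 2 warns that such records may vary between centres, and they do not capture experience. The PREMs are thus the only patient-reported evidence on the therapy experienced, and no more than that.
- A reader might infer that chance and real change could not be told apart. Descriptive analysis does not exclude SDs or intervals, and means, SDs and counts would let a reader derive them. The plan simply does not commit to them.
- A reader might infer that PREMs will be read centre by centre or item by item. The article does not say so. The per-centre figures apply only if someone reads them that way, which is plausible because each centre develops its own action plan.

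The reply does not remove the mismatch between a comparative purpose and a method named without any measure of error.

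**Conclusion.** The point holds as a minor one. The plan sets up a before/after patient comparison and commits only to describing it. At an assumed item SD of 1.0, differences of up to about 0.23 to 0.25 points pooled, or 0.40 to 0.43 points in one centre, are compatible with no change. Over SDs of 0.7 to 1.2 the ranges are 0.16 to 0.30 pooled and 0.28 to 0.52 per centre. These figures rest on the assumed SD and on PREM response between the evaluable and recruited targets.

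It would go too far to say that the PREM results will be uninterpretable or that the main trial conclusion is at risk; the primary PAHCO analysis does not use them. Nor would an interval settle causation. It covers chance only, not the cohort, historical and seasonal effects that the Discussion acknowledges for this design.

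**What to change.** Split the sentence in the Implementation study, Data analysis, into two.
- Implementation-status questionnaire: descriptive, as now.
- PREMs: report the intervention-minus-control difference with its 95% confidence interval from a centre-adjusted model as the main summary. A linear model suits a mean score, and a proportional-odds model suits single items. Give per-centre differences with their intervals as supportive estimates only, without a significance rule per centre. State that the intervals do not cover the period effects named in the Discussion.

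The cost is a sentence or two and one further model. Group and centre already enter the primary analysis, and the PREMs are collected in the same T1 survey, so no additional patients or measurements are needed.
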